## Abstract

**Background:**

Previous studies regarding rhythm control in patients with atrial fibrillation (AF) could not sufficiently demonstrate the efficacy of available anti-arrhythmic drugs. ‘Upstream therapy’ has emerged as a potential strategy for the prevention and treatment of AF. The use of angiotensin II receptor blockers and statins has been suggested to decrease new-onset AF, but which remains inadequately explored. This study was designed to examine whether valsartan or fluvastatin can reduce the risk of non-permanent AF in patients with hypertension.

**Methods/design:**

The VF-HT-AF study is a multicenter, randomized, open-label, four-arm parallel group study with comparative evaluation of valsartan and fluvastatin as upstream therapies for the treatment of non-permanent AF complicated by hypertension. The primary outcome measure is change in the development of paroxysmal AF into persistent or permanent AF, the development of persistent AF to permanent AF, and change in incidence of overall and persistent AF recurrence, as evaluated by 7-days ambulatory electrocardiograph monitoring (Holter) and patients’ diaries during 2 years’ follow-up. Secondary outcome measures of this study include the occurrence of: (1) fatal and nonfatal myocardial infarction; (2) heart failure (New York Heart Association stage III or IV); (3) cardiogenic shock; (4) serious bleeding necessitating hospitalization; (5) malignant ventricular arrhythmia; (6) revascularization therapy; (7) radiofrequency catheter ablation of AF; (8) changes of left atrial dimension, as measured by ultrasound echocardiography; (9) stroke; (10) cardiovascular mortality; and (11) all-cause mortality. A total of 1879 patients will be investigated from 15 medical centers throughout China to obtain the relevant information.

**Discussion:**

This is the first study in hypertensive patients complicated non-permanent AF in the Chinese population. Results of this study will inform the use of upstream therapies of AF.

**Trial registration:**

chictr.org, ChiCTR-TRC-12002642

**Electronic supplementary material:**

The online version of this article (doi:10.1186/s13063-015-0836-5) contains supplementary material, which is available to authorized users.

## Background

Atrial fibrillation (AF), the most common clinically significant cardiac arrhythmia, is associated with increased mortality and morbidity [1, 2], especially in hypertensive patients [3]. In general, hypertension is the most important risk factor for AF. Although much effort has been put into the development of an effective pharmacological treatment, several trials conducted in the USA and Europe proved that existing traditional anti-arrhythmic drugs failed to improve the prognosis of patients with AF [4–7].

Several systematic reviews and meta-analyses have confirmed anti-arrhythmic efficacy while raising concerns about adverse events and mortality [8]. In the past few years, a number of trials investigating upstream therapy for the prevention of AF have been reported [9]. Upstream therapies are long-term modulators of atrial remodeling regarding structure or function, which may change molecular expression contributing to the arrhythmia. The renin-angiotensin system (RAS) is an important therapeutic target for atrial remodeling. Angiotensin II receptor blockers (ARBs) have recently been reported to suppress AF recurrence in both paroxysmal and persistent AF in selected patients. However, recent placebo-controlled, double-blind trials with ARBs failed to show convincing results [10, 11]. Statins, as a well-established secondary prevention benefit for atherosclerotic coronary artery disease, are hypothesized to be beneficial against atrial arrhythmia, yet the data are inconsistent [12–15]. In addition, there have been little prospective and randomized studies to evaluate the effectiveness of upstream therapeutic strategies in hypertensive patients with non-permanent AF.

To confirm the effectiveness of ARBs or statins on AF in hypertensive patients, the Upstream Therapeutic Strategies of Valsartan and Fluvastatin on Hypertensive Patients with Non-permanent AF (VF-HT-AF study) will be conducted, with 1879 participants from 15 centers.

## Methods/design

The VF-HT-AF study is designed as a prospective, randomized, open-label, four-arm parallel, and multicenter study. The objective of the study is to test the hypothesis that upstream therapy using valsartan or fluvastatin is more effective in reducing the recurrence of AF and the progress from non-permanent AF to permanent AF in hypertensive patients with non-permanent AF, compared with conventional antihypertensive therapy using dihydropyridine calcium channel blockers (CCBs). This study will be conducted according to the principles outlined in the Declaration of Helsinki. Written informed consent will be obtained from all patients prior to the study. The study protocol has been approved by the ethics committee of the Second Hospital of Tianjin Medical University (Clinical ethical review, 2012, No. 27) as well as other participating medical centers, which are secondary or tertiary healthcare providers in China, and should provide proof of laboratory quality control. The ethical bodies that approved our study in the various centers are listed in Additional file 1. If there is any amendment to the protocol, approval must again be sought from the ethics committee. The study is registered with the Chinese Clinical Trial Registry (ChiCTR-TRC-12002642). The protocol design is based on the Consolidated Standards of Reporting Trials (CONSORT) and Standard Protocol Items: Recommendations for Interventional Trials (SPIRIT, see Additional file 2), and study results will be reported according to these guidelines.

### Patient population and entry criteria

Patients enrolled in the study need to meet the inclusive recruited criteria: (1) have hypertension, defined as an average systolic blood pressure ≥140 mmHg (1 mm Hg = 0.133 kPa) or a diastolic blood pressure ≥90mmHg (but a systolic blood pressure <180 mmHg and a diastolic blood pressure <110 mmHg) at the first visit, or the requirement of any anti-hypertension treatment at enrollment; (2) a history of non-permanent AF within 1 year prior to the enrollment, as confirmed by electrocardiography (ECG), and converted to sinus rhythm; (3) have not taken ARBs or angiotensin-converting enzyme inhibitors (ACEIs) as well as statins in the previous 2 weeks, or are taking ARBs, ACEIs and statins, but can accept a 2-week washout period; (4) aged 25–79 years; and (5) willing to sign the informed consent form (Additional file 3).

The exclusion criteria are: (1) persistent AF with a duration ≥1 year or permanent AF; (2) serious left main coronary artery disease identified by coronary angiography; (3) heart failure (New York Heart Association [NYHA] stage III or IV); (4) acute myocardial infarction in the previous 3 months; (5) surgical or interventional indications of valvular heart disease; (6) uncontrolled thyroid disease (abnormal free T3, free T4, or thyroid stimulating hormone, or requiring any anti-thyroid treatment at enrollment); (7) serious liver or renal dysfunction (ALT > 80 U/l, AST > 80 U/l, or creatinine > 132 μmol/l); (8) history of unstable angina pectoris; (9) stroke or transient ischemic attack within the previous 3 months; (10) poor treatment compliance, such as central nervous system or mental illness, or a possibility of being uncooperative in the follow-up period; (11) have taken ARBs, ACEIs or statins but cannot accept a 2-week washout period; (12) obvious hyperlipidemia that must be treated by statins or fibrates; (13) contraindication of statins or ARBs; (14) pregnancy or the possibility of pregnancy, or breast feeding; and (15) aged younger than 25 or older than 79 years.

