### Study design

The VF-HT-AF study is a randomized, multicenter, open-label, and four-arm parallel study to evaluate the effectiveness of valsartan, fluvastatin or a combination of both on recurrent AF in hypertensive patients with non-permanent AF in China. After providing informed consent, patients will be randomly assigned using a computer system to one of four groups (the valsartan group, the fluvastatin plus dihydropyridine CCBs group, the valsartan plus fluvastatin group, and the dihydropyridine CCBs group) by the School of Public Health of Tianjin Medical University, initially in a 1:1:1:1 ratio. Physicians, who should be qualified medical practitioners, screen and follow up the patients in hospital outpatient or inpatient clinics. All patients’ data will be collected using a standard case report form and transmitted to the central database at the data center. All centers will be regularly monitored for source data documentation. Missing or questionable data will be completed and corrected by queries.

If the candidate patients have not taken ARBs, ACEIs or statins in the past at least 14 days, they will be directly enrolled and randomized. If the candidate patients have taken ARBs, ACEIs or statins, they will be randomized after a 14-day washout period. Baseline data will be collected after the washout period.

The initial dose of fluvastatin will be 40 mg/day at night, while valsartan will be prescribed initially at 80 mg/day. The fluvastatin dose will be no less than 40 mg/day and that of valsartan will be no less than 80 mg/day during the follow-up period. Blood pressures in each group must reach the target blood pressure, which is set at <140/90 mm Hg.

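### The <180/<110 mmHg entry ceiling covers only one of the two routes through inclusion criterion 1, so a patient on antihypertensive treatment can enter above it

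*Protocol article*

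**What the plan says.** In the protocol article, under Patient population and entry criteria, inclusion 1 defines hypertension by two alternatives.

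- **Reading route.** An average systolic pressure of at least 140 mmHg or a diastolic pressure of at least 90 mmHg, qualified in parentheses by "but a systolic blood pressure <180 mmHg and a diastolic blood pressure <110 mmHg".
- **Treatment route.** The sentence goes on "at the first visit, or the requirement of any anti-hypertension treatment at enrollment". No pressure is given for this alternative.

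Inclusion 3 also admits patients who "are taking ARBs, ACEIs and statins, but can accept a 2-week washout period". Under Study design, "they will be randomized after a 14-day washout period" and "Baseline data will be collected after the washout period". The same section sets the on-study goal: "Blood pressures in each group must reach the target blood pressure, which is set at <140/90" mmHg.

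**The concern.** The authors print a threshold above which they evidently did not want patients to enter, but the sentence applies it to one route only. A site following the text would turn away a patient who qualifies solely on a reading above the limit, and could accept a patient already on treatment with the same reading. The second patient is above the limit despite therapy.

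Two things are at stake: the safety of patients randomised at a pressure that the protocol elsewhere rules out, and a consistent definition of the population across 15 centres.

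**Working it through.** No calculation in the protocol is in question. The check is one of logic, followed by a search for any other limit.

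**1. The criterion as a logical expression**

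- A = (systolic ≥140 or diastolic ≥90) and systolic <180 and diastolic <110, at the first visit.
- B = requirement of antihypertensive treatment at enrolment.
- Inclusion 1 is met if A or B is true.

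The parenthesis with the ceiling stands before the words that fix the first visit, and before the comma and conjunction that open B. It therefore qualifies A only: 1 of 2 routes.

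**2. What B means**

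Exclusion 6 uses a parallel phrase, "requiring any anti-thyroid treatment at enrollment", which most naturally describes a patient on treatment at entry. B is read here in the same way.

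**3. Illustrative patients (readings in mmHg)**

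- Treated, 130/80: A false, B true. Eligible, as one would expect of a treatment route.
- Treated, 150/95: A true, B true. Eligible.
- Treated, 185/112: A false because the ceiling is breached, B true. Inclusion 1 is met.
- Untreated, 185/112: A false, B false on the reading in step 2. Not eligible.

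The third patient shows the gap.

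**4. Does anything else shown restore the limit?**

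- Exclusions 1 to 15: 0 of 15 state a blood pressure value or name severe hypertension. The nearest is exclusion 13, a contraindication to statins or ARBs, which does not mention blood pressure.
- Study design: the <140/90 mmHg figure is a treatment goal, not an entry condition.
- Follow-up: blood pressure is recorded at each follow-up, with no entry limit.

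**5. Distance from target**

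- Systolic: 180 − 140 = 40 mmHg.
- Diastolic: 110 − 90 = 20 mmHg.

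A patient let through exceeds the target boundary by at least one of these amounts.

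**6. Link with the washout**

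A patient taking an ARB or ACEI for hypertension meets B, so the printed ceiling does not bind that patient. The drug is then stopped for 14 days before randomisation. The only time point printed for the ceiling is the first visit, which for these patients most naturally precedes the washout. No limit is printed for the post-washout reading on either route, so that absence is a separate matter from the gap in B.

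**The case against.** The strongest reply is that this is loose wording in a condensed article. A treatment route usually exists to admit treated patients whose pressure is below 140/90 mmHg, and the ceiling was probably meant for everyone. Fig. 1, whose legend defines BP, is not shown, and neither is the full protocol; either could contain a check for all candidates. The intent is plausible, and such a check would close the gap in practice. The printed criterion would still be wrongly scoped. This is a stated rule attached to the wrong place, not a detail left to a longer document.

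The second reply concerns harm, and most of it stands. Every arm contains valsartan or a dihydropyridine CCB, with a common target. Only ARBs, ACEIs and statins are withdrawn, and nothing printed forbids substitute treatment during the 14 days. Qualified physicians screen patients, and a safety monitoring board exists. None of this is an entry limit, but it makes serious harm less likely.

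Three stronger readings should be resisted.

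- A reader might infer that an untreated patient above 180/110 mmHg also qualifies because such a patient needs treatment. The wording does not exclude that reading, but the parallel with exclusion 6 points to current treatment, so it is not claimed.
- A reader might infer that the sponsor chose to enrol patients with severe hypertension. Nothing in the article shows such a choice.
- A reader might treat the washout as the source of the gap. It is not: the treatment route lacks a ceiling with or without it, and the missing post-washout limit affects patients on the reading route too.

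**Conclusion.** The point holds as a minor flaw in safety and population definition. As printed, the ceiling binds only patients who enter on the first-visit reading, and a treated patient at or above 180 mmHg systolic or 110 mmHg diastolic meets inclusion 1 with no exclusion to stop entry.

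The number of such patients cannot be estimated from the article. The only sizes available are the minimum distances from the target boundary, 40 mmHg systolic or 20 mmHg diastolic.

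A reader might infer that the comparison is compromised. It is not: eligibility is settled before randomisation and is the same for all four arms, so the gap introduces no bias between arms and leaves the sample size and analysis unchanged.

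The conclusion assumes that the treatment route means patients on antihypertensive therapy at entry, and that no check outside the printed text already applies the ceiling to them.

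**What to change.** Apply the ceiling to both routes. The simplest form is one added exclusion for all candidates: systolic ≥180 mmHg or diastolic ≥110 mmHg. This is the exact complement of the protocol's own limit and introduces no new threshold.

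As a separate safety step, check the same limit at the post-washout baseline in patients whose ARB or ACEI was withdrawn. Baseline data are already collected then, so no extra visit is needed. This step goes beyond repairing the sentence, because it adds a time point the protocol does not print and may exclude patients whose pressure rose because of the washout. The sponsor can decide on it separately.

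The cost is a few more screen failures, some of them after a completed washout if the second step is adopted, and an amendment, for which "approval must again be sought from the ethics committee". The article describes the trial as still recruiting, so the change could protect patients yet to be enrolled.

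### Exclusion 12 screens out a statin need only when it comes from obvious hyperlipidemia, so patients taking a statin for an older infarction or stable coronary disease can be washed out and randomized to an arm with no study statin

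*Protocol article*

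**What the plan says.** All references are to the protocol article.

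**Patient population and entry criteria.** Inclusion 3 admits patients off these drugs for 2 weeks, "or are taking ARBs, ACEIs and statins, but can accept a 2-week washout period". Exclusion 11 is its mirror image and removes those who "have taken ARBs, ACEIs or statins but cannot accept a 2-week washout period". The only criterion that asks whether a patient needs a statin is exclusion 12: "obvious hyperlipidemia that must be treated by statins or fibrates". The coronary exclusions are "serious left main coronary artery disease identified by coronary angiography" (2), "acute myocardial infarction in the previous 3 months" (4) and "history of unstable angina pectoris" (8).

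**Study design.** "If the candidate patients have taken ARBs, ACEIs or statins, they will be randomized after a 14-day washout period". There are four arms, initially in equal ratio. Two contain fluvastatin (with a CCB, or with valsartan) and two do not (valsartan, CCB).

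**Follow-up.** It lasts 2 years. The doses and types of other lipid-lowering drugs are recorded; nothing in the article prohibits them.

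**Background.** The rationale for the statin arms begins "Statins, as a well-established secondary prevention benefit for atherosclerotic coronary artery disease".

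**The concern.** The protocol already recognises that some patients need a statin and should not be randomized, but it ties that need to lipid level alone. The section on fluvastatin in the Discussion gives a lipid-based reason: it is unclear whether a statin effect on AF depends on lipids. That explains the wording but leaves the coronary indication uncovered.

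For a patient with such an indication, the entry rule stops the drug and half of the arms do not replace it. One of two things then follows. If the patient stays off a statin, an indicated drug is missing while myocardial infarction, revascularization and cardiovascular death are being counted as secondary outcomes. If a non-study statin is restarted in a no-statin arm, the comparisons that isolate fluvastatin become less distinct. These are alternatives for any one patient, and both start from the same eligibility rule.

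**Working it through.** The plan gives no figure of its own on this point, so there is none to reproduce. The check is a reading of the criteria followed by short arithmetic.

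**Step 1: is such a patient eligible?** Take a hypertensive patient with non-permanent AF who takes a statin after an infarction 2 years ago, with no unstable angina, no serious left main disease and no obvious hyperlipidemia, and who meets the other criteria.
- Exclusion 2: not met.
- Exclusion 4: not met, because the window is 3 months.
- Exclusion 8: not met.
- Exclusion 12: not met, because the statin need is not due to hyperlipidemia.
- Exclusion 11: not met if the patient accepts 2 weeks off the drug.
- Inclusion 3: met on the same condition.

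The patient is eligible. The same holds for stable coronary disease outside the left main.

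**Step 2: chance of an arm without a study statin.** Arms without fluvastatin / all arms = 2 / 4 = 50%. This applies to the stated starting ratio.

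**Step 3: what exclusion 11 tests.** Washout / follow-up = 14 / (2 × 365) = 14 / 730 = 1.9%. Acceptance of the washout covers about 2% of the length of follow-up and is not tied to the reason for the statin.

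**Step 4: scale.** The article gives no prevalence of coronary disease, so the share f of randomized patients in this group is unknown. Expected number in the no-statin arms = f × N × 0.5. With f = 1%, chosen only as a unit:
- N = 1404 (the required number in Sample size calculation): 0.01 × 1404 × 0.5 = 7.0
- N = 1879 (the total planned): 0.01 × 1879 × 0.5 = 9.4

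Both scale in proportion to f.

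**Step 5: which comparisons a restart touches.** A restart in the CCB arm dilutes CCB plus fluvastatin versus CCB, the comparison on which Expected implications rests the fluvastatin claim. A restart in the valsartan arm dilutes the combination versus valsartan. Valsartan versus CCB has no fluvastatin effect to dilute, as neither arm has a study statin. As a rough scale, assume that a restarted statin acts like fluvastatin and that risks are otherwise equal. If a proportion r of the group restarts, the expected difference shrinks by the factor (1 − f × r). With f = 1% and r = 1 this is 0.99, a loss of 1% of the difference. Neither f nor r can be taken from the article.

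**The case against.** The strongest reply is that the only interruption the protocol imposes is 14 days, on a patient who agrees to it. Qualified physicians do the screening and can keep out someone who should not stop a statin. Consent, ethics review and a safety monitoring board are in place. Other lipid drugs are foreseen in follow-up, and treatment is open-label, so a physician can see that no study statin is assigned and prescribe one. A rule on concomitant drugs is the kind of detail an article leaves to the full protocol. The group is also narrowed by exclusions 2, 4, 8, 11 and 12, and its size is unknown.

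Much of this stands, and it limits the point:
- A reader might infer that the protocol keeps these patients off statins for 2 years. It does not; it neither forbids nor provides for a restart.
- A reader might infer bias or a power shortfall. Neither follows. Randomization keeps every comparison valid, and Sample size calculation states no power for a fluvastatin comparison.
- A reader might see a contradiction with the assurance about control participants in Compliance strategy, or with the ethical argument for antihypertensive treatment in Expected implications. The first is loose reassurance. The second is about blood pressure and silent on statins. Neither is a commitment that the entry rule breaks. The Background statement is likewise motivation and not a rule, though it does show the protocol's own view of the drug.

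What does not stand is that an unseen concomitant-drug rule would settle the matter. If it bars a restart, the patient lacks an indicated drug; if it allows one that is used, the fluvastatin comparison is diluted. Only the eligibility rule can avoid both, and that rule is stated in the article. Physician discretion under exclusion 11 is a partial safeguard that concerns 2 weeks and not the indication.

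**Conclusion.** The point holds as a gap in the entry criteria that should be fixed. Patients on a statin for an older infarction or stable coronary disease outside the left main, without past unstable angina, are eligible if they accept the washout. They lose the drug for 14 days and have a 50% chance of an arm with no study statin. What is at stake is patient protection and a clean fluvastatin comparison.

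The conclusion rests on the criteria as printed and on the starting allocation ratio. The number affected is unknown: about 7 of 1404 or 9 of 1879 in the no-statin arms for each 1% of patients in the group. If few such patients are enrolled, both consequences are small in aggregate, though the matter remains for each of them. Confidence is medium for that reason.

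**What to change.** Extend exclusion 12 to read: "obvious hyperlipidemia that must be treated by statins or fibrates", or an established coronary secondary-prevention indication for which the patient needs a statin (for example prior myocardial infarction or coronary revascularization). Tying the clause to a need for a statin matters, since excluding everyone with documented coronary disease would be broader than the problem requires.

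Trial status says that recruitment is under way. For patients already enrolled who meet the new wording:
- have the treating physician review the need for a statin, and allow an indicated statin in any arm;
- add one sensitivity analysis without them, selecting patients on the indication at entry and not on whether a statin was restarted later, so that the arms stay comparable.

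A lighter alternative is to keep such patients eligible and state that an indicated statin may be resumed. That protects the patient but accepts dilution of the fluvastatin comparisons, so the exclusion is preferable for new patients.

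The cost is one amendment with renewed ethics approval, a somewhat narrower and less general population, one review per affected enrolled patient, and one extra analysis.
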